# The TELEhealth Shared decision-making Coaching and Navigation in Primary carE (TELESCOPE) intervention: a study protocol for delivering shared decision-making for lung cancer screening by patient navigators

**DOI:** 10.21203/rs.3.rs-4254047/v1

**Published:** 2024-04-22

**Keywords:** Shared decision-making, lung cancer screening, lung neoplasms, tobacco treatment, study protocol, cluster randomized controlled trial, telehealth, patient navigation, primary care, enhanced usual care

## Abstract

**Background:**

Lung cancer screening (LCS) can reduce lung cancer mortality but has potential harms for patients. A shared decision-making (SDM) conversation about LCS is required by the Centers for Medicare & Medicaid Services (CMS) for LCS reimbursement. To overcome barriers to SDM in primary care, this protocol describes a telehealth decision coaching intervention for LCS in primary care clinics delivered by patient navigators. The objective of the study is to evaluate the effectiveness of the intervention and its implementation potential, compared with an enhanced usual care (EUC) arm.

**Methods:**

Patients (n = 420) of primary care clinicians (n = 120) are being recruited to a cluster randomized controlled trial. Clinicians are randomly assigned to 1) TELESCOPE intervention: prior to an upcoming non-acute clinic visit, patients participate in a telehealth decision coaching session about LCS delivered by trained patient navigators and nurse navigators place a low-dose CT scan (LDCT) order for each TELESCOPE patient wanting LCS, or 2) EUC: patients receive enhanced usual care from a clinician. Usual care is enhanced by providing clinicians in both arms with access to a Continuing Medical Education (CME) webinar about LCS and an LCS discussion guide. Patients complete surveys at baseline and 1-week after the scheduled clinic visit to assess quality of the SDM process. Re-navigation is attempted with TELESCOPE patients who have not completed the LDCT within 3 months. One month before being due for an annual screening, TELESCOPE patients whose initial LCS showed low-risk findings are randomly assigned to receive a telehealth decision coaching booster session with a navigator or no booster. Electronic health records are abstracted at 6, 12 and 18 months after the initial decision coaching session (TELESCOPE) or clinic visit (EUC) to assess initial and annual LCS uptake, imaging results, follow-up testing for abnormal findings, cancer diagnoses, treatment, and tobacco treatment referrals. This study will evaluate factors that facilitate or interfere with program implementation using mixed methods.

**Discussion:**

We will assess whether a decision coaching and patient navigation intervention can feasibly support high-quality SDM for LCS and guideline-concordant LCS uptake for patients in busy primary care practices serving diverse patient populations.

**Trial Registration::**

This study was registered at ClinicalTrials.gov (NCT05491213) on August 4, 2022.

## BACKGROUND

Lung cancer is the leading cause of cancer death among US men and women, with 21% of all cancer deaths attributed to lung and bronchus cancers. ^1^ When non-small cell lung cancer, the most common type of lung cancer, is detected at the localized stage, the 5-year survival rate is 65%, compared with 37% and 9% at the regional and distant stages respectively. ^2^ Hence, lung cancer screening (LCS) leading to early detection and treatment of lung cancer can reduce lung cancer mortality. Low-dose computed tomography (LDCT) is currently the only screening modality found to reduce lung cancer mortality. ^3^ In 2011, the National Lung Screening Trial (NLST) concluded that screening using LDCT reduced lung cancer mortality by 15–20% compared with using chest radiography. ^3–5^ While LCS using LDCT reduced lung cancer mortality, there were potential harms associated with the screening, including false positive tests, the need for additional testing, possible complications from invasive diagnostic procedures, radiation exposure, overdiagnosis, and incidental findings. ^6^

In 2013, the United States Preventive Services Task Force (USPSTF) issued a Grade B recommendation for LCS using LDCT for individuals age 55–80, who currently smoke or quit smoking within the past 15 years, and who have at least a 30 pack-year smoking history. ^7^ The USPSTF encouraged shared decision-making (SDM) between patients and providers, including a discussion of the potential benefits, harms, and limitations of LCS. ^7^ The 2015 Centers for Medicare & Medicaid (CMS) coverage determination allows for reimbursement of the LDCT for LCS using the same smoking history criteria as the USPSTF but limiting the upper age for screening to 77. ^8^ They also issued an unprecedented coverage requirement that beneficiaries must undergo SDM and counseling delivered by a licensed independent practitioner before screening is offered. ^8^ In 2021, the USPSTF updated their LCS recommendation by lowering the starting age to 50 years and reducing the pack-year threshold to 20. ^9^ These new criteria expanded the pool of eligible persons, particularly high-risk persons of color and women. ^10^ In 2022, CMS updated their coverage determination to align with the new USPSTF criteria for starting age and pack-years. The SDM and counseling visit remains a requirement for CMS reimbursement for the patient’s first LCS, but can now be delivered by a non-clinician and via telehealth. ^11^

LCS uptake has increased slowly since the publication of the NLST main findings, but screening rates remain suboptimal with national estimates of LCS rates among screen-eligible populations ranging from 14.4–21.1%.^12–15^ Clinicians report important barriers to implementing LCS, such as being unfamiliar with screening guidelines, difficulties in identifying eligible patients, lack of training in SDM, lack of time to conduct SDM discussions, competing clinical demands, and need for more support in managing follow-up testing or abnormal results. ^16–18^ Patient barriers include being unaware of the purpose of LCS, not being offered screening, fear of cancer diagnosis, limited access to health care, experiences of smoking-related stigma, and mistrust of the health care system. ^18,19^ These barriers are particularly problematic for underrepresented minorities, people of low socioeconomic status, and rural populations. ^19^ While some experts have attributed the SDM requirement in CMS coverage as being a barrier to screening, ^20,21^ a high quality SDM process has been found to increase patient knowledge about LCS, decrease decisional conflict, increase the likelihood of adherence to screening guidelines, and is aligned with the principle of respecting patient autonomy. ^20,22–24^ Unfortunately, there is evidence that SDM conversations for LCS are not routinely carried out, and many do not meet the minimum criteria for SDM. ^25,26^ Moreover, the potential harms of LCS were infrequently discussed. ^25,26^

To address the deficiencies in SDM, we designed an intervention where decision coaching for LCS is delivered by patient navigators via telehealth to patients recruited from primary care clinics (TELEhealth Shared decision-making COaching and navigation for lung cancer screening in Primary carE [TELESCOPE]). This study builds on our prior work. Our team developed and tested an LCS decision coaching intervention using trained decision coaches and a patient decision aid targeting tobacco quitline callers. ^24,27^ The intervention increased knowledge and improved decision quality. ^27^ This decision coaching intervention is adapted for the TELESCOPE intervention for patients in primary care settings. Delivering decision coaching and navigation via telehealth by patient navigators is a potentially scalable and efficient approach to meeting expectations for delivering SDM and facilitating guideline-concordant screening. In addition, identifying potentially eligible patients from primary care clinics and offering an SDM process can ensure that minority populations are being included in efforts to educate and engage patients in LCS.

### Aims

The trial’s aims are to: (1) test the effectiveness of a decision coaching intervention for LCS delivered by patient navigators (TELESCOPE) versus EUC (enhanced usual care delivered by their primary care provider) on: a) quality of the SDM process about LCS (primary outcome); b) initial LCS uptake and subsequent adherence to annual LCS; and c) tobacco treatment referrals and receipt of tobacco treatment for current smokers; d) assess potential mediators and moderators of intervention effects; and (2) evaluate the implementation potential of patient navigator-delivered decision coaching for LCS by identifying organizational-, clinician-, and patient-level factors that might be barriers or facilitators to successful implementation.

## METHODS

This study protocol is prepared in accordance with The Standard Protocol Items: Recommendations for Interventional Trials (SPIRIT) statement. ^28^ Please see Additional File 1 for the completed SPIRIT checklist and Fig. 1 for the flow of patients and patient data collection for the TELESCOPE trial. The study results will be reported in line with the Consolidated Standards of Reporting Trials (CONSORT) statement for cluster randomized controlled trials (RCTs) ^29,30^ and the implementation outcomes will be reported using the Standards for Reporting Implementation Studies (StaRI) checklist^31^.

### Conceptual Framework

This trial uses an effectiveness-implementation hybrid type I design and is guided by the Practical, Robust Implementation and Sustainability Model (PRISM) as the implementation framework. ^32,33^ PRISM accounts for the role of organizational and patient perspectives, external environment, implementation and sustainability infrastructure, and recipient characteristics in the success of an intervention. ^33^ The impact of the intervention will be evaluated using the constructs in the RE-AIM (reach, efficacy, adoption, implementation, and maintenance) framework, which is a component of PRISM. ^33^ The TELESCOPE intervention uses the implementation strategy of ‘revising professional roles’ by training patient navigators to lead the SDM discussion because clinicians often lack the time and training to provide high quality SDM during clinic visits. ^34^

### Design

Figure 2 shows an overview of the TELESCOPE study design. We are conducting a cluster RCT with primary care clinicians as the unit of randomization into either (1) the TELESCOPE intervention arm, or (2) an EUC arm. Patients of clinicians in the TELESCOPE arm receive the decision coaching intervention delivered by trained patient navigators (hereafter referred to as ‘decision coaching session’) prior to an upcoming clinic visit with their primary care clinician. Patients of clinicians in the EUC arm have the opportunity to participate in an LCS discussion with their primary care clinician at an upcoming clinic visit. Usual care is enhanced by providing clinicians in both the TELESCOPE and EUC arms with access to a Continuing Medical Education (CME) webinar about LCS and an LCS discussion guide. Patients in the TELESCOPE arm who complete initial screening with negative or benign findings are due for their next screening in 12 months. Half of these participants are randomized to receive a telehealth decision coaching booster session with a patient navigator 1 month before their next annual screening. Table 1 provides a summary of components for the TELESCOPE and EUC arms, which are described in greater detail below.

For the TELESCOPE Trial, a community advisory board of diverse community stakeholders reviews and guides intervention development, recruitment strategies, study procedures, patient-facing materials (e.g., study flyers, informed consent forms, surveys, intervention materials), implementation (e.g., patient recruitment, retention, cultural acceptability), interpretation and dissemination of the results, and identification of next steps.

### Setting and Primary Care Clinicians

The TELESCOPE intervention is implemented remotely through community-based primary care sites affiliated with the RWJBarnabas Health (RWJBH) system, and from academic primary care sites including the Rutgers Robert Wood Johnson Medical School and the Rutgers New Jersey Medical School. RWJBH leadership, academic primary care site leadership, practice administrators, and lead clinicians endorsed involvement of clinicians in the TELESCOPE study. All clinicians (i.e., family medicine physicians, internal medicine physicians, nurse practitioners, physician assistants) from these sites received an initial introduction email from the research team about the TELESCOPE study. For RWJBH clinicians, the study was presented by the clinician administrators at organizational huddles and weekly meetings, and newsletters that described the study were emailed to all clinicians. In line with institutional guidelines, clinicians at academic sites are invited to participate in the study using an opt-out strategy, and non-academic RWJBH clinicians are invited to the study using an opt-in approach. An estimated 120 primary care clinicians (60 in each arm) from 40 statewide primary care sites are participating in the study.

### Patient Eligibility Criteria

Eligibility for this study is based on CMS criteria for LCS to ensure insurance coverage. ^11^ Patients are eligible if they: (1) are aged 50 to 77 years; (2) currently smoke or have quit smoking within the past 15 years; (3) report a 20 or greater pack-year smoking history; (4) are able to speak English; and (5) are scheduled for a non-acute care visit with one of the study clinicians. Individuals are excluded if they have a history of lung cancer, had undergone a chest CT in the past 12 months, have hemoptysis, or their clinician deems them as unable to undergo LCS or subsequent treatment for lung cancer (e.g., being in poor health).

### Patient Recruitment and Enrollment

Using the Epic electronic health record (EHR), study staff identify patients who have an upcoming non-acute clinic appointment with a participating clinician in the next 2 months and who are potentially eligible for the study based on their age and smoking history. Subsequently, participating clinicians are emailed a list of their patients who are potentially eligible and asked to identify and notify study staff within 1 week if any patients on the list should not be contacted to participate in the study. Study staff then send approved potential patient participants a study invitation email containing a link to the pre-screening eligibility form. We also developed a 1-page recruitment flyer with culturally relevant images of patients, key eligibility criteria for the study, study activities, benefits of participating in the study, and study team contact information. The recruitment flyer is sent out to potential patient participants by email (if their email addresses are available), regular mail, and via the Epic patient portal (if their portal is activated). Subsequently, study staff reach out via telephone to potential patient participants to introduce the TELESCOPE study, answer questions, assess interest in participating, determine LCS eligibility, and consent eligible patients who are willing to participate. We employ evidence-based practices for enhancing recruitment and retention including incentives, an interculturally competent recruitment flyer, study specific community advisory board, persistence, skilled teamwork, and an interculturally competent staff. ^35–37^

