### Randomization

Participating clinicians are randomized 1:1 to either the TELESCOPE or EUC arm, with stratification based on primary practice affiliation at an RWJBH Primary Care Network or a Rutgers academic primary care practice site, and whether the clinician is a family medicine or internal medicine practitioner. Randomization of clinicians is done by the study’s biostatistician (SS) using STATA. After stratification, randomization is constructed within each stratum with random block sizes ranging from 2 to 6. We cannot blind clinicians or patient participants to the intervention. Patient participants are blinded to the study’s specific hypotheses; statisticians and outcome assessors are blinded to the allocation.

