### TELESCOPE Intervention

Immediately after completing the baseline survey (T0), patients in the TELESCOPE arm are sent the 2-page LCS Discussion Guide and the Decision Coaching Slides via regular mail, and a link to the virtual meeting (Zoom or Microsoft Teams) at their preferred date and time. The decision coaching session is conducted over the phone with patients who do not have internet access. During the decision coaching session, patient navigators follow the scripted Decision Coaching Manual. The script begins with patient navigators introducing themselves and the purpose of the session, and then sharing their computer screen with patients to show the Decision Coaching Slides. Patient navigators review the slides’ content with the patient which includes lung cancer survival rates, importance of yearly LCS, how LCS is performed using an LDCT, potential benefits of LCS (finding lung cancer early and the magnitude of the benefit), and the potential harms of LCS (false alarms, need for additional testing, radiation exposure, overdiagnosis, and incidental findings).

After informing patients of the benefits and harms of LCS, the patient navigator stops sharing their screen and explores the patient’s thoughts about screening, barriers, and screening preferences. Patient navigators are trained in active listening techniques from motivational interviewing to ensure that the patient’s questions, barriers, and concerns are addressed. ^38^ If the patient indicates that she/he wants to be screened, the patient navigator helps identify the patient’s preferred screening location. If patients are unsure or do not want to be screened, the patient navigator advises them to discuss LCS and their concerns with their clinician at their upcoming clinic visit. Finally, the patient navigator assesses patients’ current smoking status, discusses the importance of not smoking, and offers to connect them with a Tobacco Treatment Program.

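### Unblinded clinicians, very probably aware of their arm, may remove their own patients from recruitment lists without a stated criterion, and the stated models adjust only for clustering or design

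*Protocol article*

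**What the plan says.** All references are to the protocol article.

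- **Unit and blinding.** Design describes a "cluster RCT with primary care clinicians as the unit of randomization". Randomization says "Participating clinicians are randomized 1:1 to either the TELESCOPE or EUC arm", stratified by practice affiliation and by family or internal medicine. It adds "We cannot blind clinicians or patient participants to the intervention", while "statisticians and outcome assessors are blinded to the allocation". Recruiting staff are not mentioned in either group.
- **Clinician review.** Patient Recruitment and Enrollment has staff search the record system for patients with a visit in the next two months. Then "participating clinicians are emailed a list of their patients who are potentially eligible and asked to identify and notify study staff within 1 week". What the clinicians are to report is worded only as "if any patients on the list should not be contacted to participate in the study". Only patients who pass this step are invited.
- **Clinician-judged exclusion.** Patient Eligibility Criteria already excludes patients whom the clinician considers unable to undergo screening or later lung cancer treatment.
- **Consent and baseline.** Staff then telephone patients to "assess interest in participating, determine LCS eligibility, and consent eligible patients who are willing to participate". The T0 survey follows consent. Under TELESCOPE Intervention, "Immediately after completing the baseline survey (T0), patients in the TELESCOPE arm are sent" the arm-specific material.
- **Analysis.** Data Analysis plans a cluster-adjusted t-test and a mixed model for the primary SDMP_4 score, and chi-square and logistic models for screening uptake. These adjust for clustering or the study design. Patient characteristics appear as moderators, and the sensitivity analysis concerns missing data. Table 2 shows SDMP_4 measured at T1 only.

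**The concern.** Randomising clinicians balances clinicians. It does not balance patients who are chosen afterwards by people who may know the arm. An open request to strike names gives an unblinded clinician room to shape who is enrolled.

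The two arms ask different things of the clinician. Under Enhanced Usual Care the clinician must lead the discussion, order the scan and follow up the result. In the TELESCOPE arm a navigator coaches the patient and an order arrives for signature. Reasons for striking a name could therefore differ by arm, although the documents do not indicate in which direction.

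If enrolled patients differ by arm in interest in screening, both the SDM score and six-month uptake could shift without any intervention effect.

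**Working it through.** **1. Is the arm known when names are struck?** The article gives no order for clinician randomisation, disclosure and listing. The indirect evidence is as follows.

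- Lists look two months ahead, while Trial Status has recruitment running from May 2023 to May 2026. Listing must therefore be repeated.
- In early April 2024, 117 clinicians were participating and 134 patients were enrolled. With a target of 420, 420 − 134 = 286 patients (286/420 = 68%) were still to come, mostly from clinicians already in the trial.
- TELESCOPE clinicians sign the orders that navigators place, so the arm becomes evident once a first patient has elected screening.
- With 120 clinicians there are at most 120 first patients. At least 420 − 120 = 300 patients (300/420 = 71%) are therefore a clinician's second or later patient, and exactly 300 if every clinician contributes at least one. Some of these may sit on the same first list, so 300 indicates exposure and does not count patients listed after disclosure.

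**2. Do the stated models absorb an imbalance?** Adjustment for clustering corrects the standard error. It does not remove a shift in the arm mean caused by different patients. With SDMP_4 absent at T0, there is no baseline value of the primary outcome to adjust for.

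**3. How large could the effect on error be?** The documents give no imbalance, so the shifts b below are assumptions. With no true effect and a two-sided 5% test, the rejection rate is Φ(−1.96 − b/SE) + 1 − Φ(1.96 − b/SE).

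Two standard errors (in SD units) are carried for the primary outcome:

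- Implied by the plan's detectable effect: 0.38 / (1.960 + 0.842) = 0.136.
- From 189 per arm, 378/120 = 3.15 patients per clinician and ICC 0.20: design effect 1 + 2.15 × 0.20 = 1.43, and SE = √(2 × 1.43/189) = 0.123. The detectable effect is then 2.802 × 0.123 = 0.345. The plan also allows for a practice-site ICC but gives no split, so 0.38 can be neither confirmed nor faulted, and nothing here depends on it.

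| Assumed shift in SDMP_4 | Error, SE 0.136 | Error, SE 0.123 |
|---|---|---|
| 0.05 SD | 6.6% | 6.9% |
| 0.10 SD | 11.4% | 12.9% |
| 0.20 SD | 31.4% | 36.9% |

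For uptake, 420/120 = 3.5 and ICC 0.04 give a design effect of 1 + 2.5 × 0.04 = 1.10, or 210/1.10 = 190.9 effective patients per arm. This reproduces the plan's power for 14% versus 25.5% (80.8% against a stated 80%). With a pooled-variance test, selection alone producing 14% versus 16%, 18% or 20% would be declared significant in about 8%, 19% or 34% of trials.

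**The case against.** The strongest reply is that much of this rests on silence in a condensed article, and part of that reply stands.

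- **Order of events.** A reader might infer that the article documents allocation as known before listing. It does not. The reach definition under Intervention Efficacy and Reach even speaks of patients as randomised to TELESCOPE, although that fits poorly with clinicians as the unit. The order remains a strong inference for later patients and is not shown for a clinician's first.
- **Recruiters.** A reader might infer that the callers know the arm. The article does not say so, and masking or scripts may be described in the full protocol. Consent before T0 is normal practice and is not a fault.
- **The removal step.** It may simply be where the clinician-judged exclusion is applied. Candidates come from one record search, clinicians do not refer patients, and a clinician who does not reply leaves the patient in. These safeguards limit the risk. They do not close it, because the search comes before the removal and the wording sets no limit.
- **Motive.** Nothing says that striking a name relieves an Enhanced Usual Care clinician of the discussion, and TELESCOPE clinicians also have tasks. No direction of bias can be claimed.
- **Covariates.** An analysis plan that is not shown may add them, and the article does not rule them out. The point is therefore about what the stated models adjust for. It is not a claim that the final analysis cannot correct.

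**Conclusion.** The point holds in a limited form. An open-ended removal step in the hands of unblinded clinicians is a stated feature of the design, and the models as stated do not address the imbalance it could cause. That the arm is known at that step is very probable for most patients, given rolling recruitment and at least 300 of 420 second or later patients, but it is inferred. Whether recruiters know the arm is unknown.

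The documents do not show that differential selection has occurred, and they give no figure for it. The error rates of about 7%, 11-13% and 31-37% depend entirely on the assumed imbalances of 0.05, 0.10 and 0.20 SD. They show only that a modest imbalance would matter. No sample-size figure changes.

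**What to change.** 1. **Analysis.** Add fixed covariates to the primary mixed model and the uptake model: T0 intention to be screened, T0 screening knowledge, age, smoking status and the two randomisation strata. All are already collected at T0, at eligibility or at randomisation, and T0 precedes delivery of arm-specific material. The cost is a few lines in the analysis plan and slightly more analysis work. It is also the only one of these three measures that reaches patients already enrolled. It cannot remove selection on unmeasured factors.
2. **Removal step.** Limit clinician removals to the exclusions in Patient Eligibility Criteria, record the reason, and report listed, removed, refused and consented patients by arm. The cost is a small logging burden. State in the same place the order of clinician randomisation, disclosure and listing.
3. **Recruiters, where workable.** Use one common script and lists without the arm until T0 is complete. Masking may erode within a clinician who contributes 3-4 patients. Study staff also chase TELESCOPE scan orders with imaging centres, so some separation of roles may be needed.
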